## Abstract

**Introduction:**

Delayed hospital discharge is a persistent care quality issue experienced across health systems worldwide and remains a priority area to be addressed in Canada. Often associated with a decrease in services while waiting to leave the hospital, delayed discharge from hospital can lead to increased frailty, physical and cognitive decline, and caregiver burnout. Optimizing availability of and timely access to community-based health and social care are avenues that could reduce initial admissions to the hospital and length of hospital stay, and facilitate hospital discharges.

**Methods:**

This research will explore the ways in which community resources could be leveraged to potentially avoid hospitalization and delayed hospital discharge for older adults using sequential mixed-methods including co-design. To better understand the characteristics and needs of older adults, the research team will first identify sub-populations of older adults (65 years old or older) at risk of hospitalization and delayed discharge using comprehensive, longitudinal administrative health data. From these health data, risk profiles and personas will be created and then shared with key partners (e.g., older adults, caregivers, healthcare providers, healthcare decision-makers), who will be engaged to identify, leverage, and create targeted care solutions. The barriers and facilitators to the implementation of these care solutions will then be explored.

**Discussion:**

Delayed hospital discharge has been a critical care quality issue across Canada for decades. The current research will provide health system leaders with an approach to better allocate services to older adults in order to avoid delayed hospital discharge and identify gaps in health and social care resources based on the characteristics, needs, and preferences of older adults, their caregivers, and providers.

## Introduction

Demands for hospital beds are high in the Canadian healthcare system [1]. There are over 3 million acute care hospitalizations in Canada each year [2], and approximately 20% of patients end up “getting stuck” in hospital following the completion of their acute medical treatment [3]. This means that while treatment is completed, non-medical considerations (often social in nature) prevent successful discharge. In Canada, this phenomenon is referred to as Alternate Level of Care (ALC) [4, 5] and more commonly referred to as delayed hospital discharge in other health systems [6]. Finding solutions to address delayed hospital discharge has been a major priority in Canada for several decades [5, 7], but the problem persists.

To address these pressures in the healthcare system, it is critical to look at how hospitalizations and delays in discharge can be avoided, especially via “continuous and coordinated care practices” upstream (p.1) [8]. Most of the research to date on delayed discharge has focused on the characteristics of patients who have delayed hospital discharge status (e.g., majority 75 years old or older, without a live-in caregiver, has co-morbidities, lower socioeconomic status) as well as strategies to improve patient flow *once they are already in hospital*. In McGilton et al.’s scoping review on transitional care programs for individuals at risk of delayed discharge, the authors highlighted the importance of improving acute or community care practices upstream rather than continuing to reactively address the individual health consequences “that occurred in hospitals” (p. 15) [9]. There is a significant gap in research focusing on the prevention of delayed hospital discharge, such as earlier access to community resources (defined as formal or informal health and social support, whether part of or independent from services offered within the healthcare system, delivered to individuals who reside outside of the hospital in a home or other community-based residence) among people at risk. Also, in previous studies, the perspectives and lived experiences of patients and caregivers are limited [9–11]. As COVID-19 and its legacy impacts have placed additional strain on hospital resources, it is even more important to explore under what conditions and for whom, hospitalization and subsequent delayed hospital discharge designation can be avoided or minimized.

Part of facilitating a better understanding of how to proactively address delayed hospital discharge is the Balance of Care approach [12, 13]. The Balance of Care was established in the United Kingdom (UK) and applied in Ontario, Canada, as a health system planning tool to optimally distribute existing resources in order to better care for aging populations [14, 15], with some studies conducted from the standpoint of aging populations with mental health conditions [16, 17], as well as senior management and frontline providers [18]. In previous research in Ontario, the Balance of Care approach has been used to address long waitlists for long-term care [19] and access to services for aging individuals in rural settings [12, 20].

The study aims to investigate how to prevent delayed hospital discharge by examining what health and social resources are needed in the community. Finding the right “balance of care” between hospital and community is required to ensure that older adults are empowered to be in the place of care that makes the most sense for their needs and preferences.

## Materials and methods

### Study objectives, design, and research questions

This is a 4-phase explanatory sequential mixed-method study. Leveraging the expertise of an interdisciplinary team in machine learning (ML), co-design, community engagement, mixed-methods, and delayed hospital discharge, the authors will address the following objectives:

Better understand the characteristics and needs of older adults (65 years of age and older) at risk of hospitalizations that lead to a delayed discharge.Understand how community resources could be leveraged to avoid hospitalization of older adults.Generate an approach to better allocate existing resources, understand the barriers and enablers in doing so, and disseminate this knowledge within communities.

The Balance of Care approach informs this research as the research team will build more in-depth knowledge of the characteristics of older adults at risk of hospitalization and co-design care packages to better understand the balance of care required to better support this population in the community and avoid hospitalization and ALC designation.

The research question for the quantitative phase is: How can supervised machine learning algorithms be developed and validated to accurately predict the risk of delayed-discharge hospitalization and identify the characteristics of older adults with such risk? The research questions for the qualitative phase are: What would community care look like for older adults at risk of being designated with delayed discharge status? What would hospital care look like for people who are at risk of being designated with delayed discharge status? What are the barriers and facilitators to providing community care as well as optimal hospital care for older adults at risk of hospitalization with a delayed discharge status?

### Ethics

The quantitative part of this research including data and related analysis are housed at and led by researchers (MZ and [name]) at a university for which there are separate ethical provisions approved by the Hamilton Integrated Research Ethics Board (HiREB; REB # 5472) in Ontario.

The qualitative portion of this research has been approved by the Research Ethics Boards at Trillium Health Partners (THP; ID#1196), Royal Victoria Regional Health Centre (RVRHC; REB # R23-039) and University of Toronto (REB #45827). Humber River Hospital (HRH) has recently established their Research Ethics Board; the authors are preparing a research ethics application for submission.

### Positionality

The research team comprises researchers who share a common goal–to improve the quality of life for aging populations in Ontario by contributing to strengthened support to avoid or minimize hospitalization, where possible. For some team members, this goal is motivated by individual lived experiences supporting people to navigate the healthcare system, while for other team members, this goal is motivated by a passion for health systems improvement. Entering into the research, the research team acknowledges each individual’s unique lived experiences and perspectives, which, alongside a recognized gap in care for aging populations, have directed the formation of this project.

Who each individual on the research team is as a researcher, including their experiences and backgrounds, has an impact on the work [21–23]. The research team holds various positions as researchers, ranging from scientists, research associates, associate professors, as well as clinicians. Team members hold diverse training in public health, psychology, social work, medicine, and physical therapy, and specialized expertise in aging populations, women’s health, quantitative, qualitative, mixed methods, and the balance of care approach. The authors acknowledge the privilege entwined in their positions as researchers in university and hospital settings, with the potential to make positive changes for aging populations and providers who care for this population. This contributes to the power dynamic between themselves as researchers and potential aging participants who may be experiencing instability.

As team members enter into the research, they will continue to engage in reflexive conversations about their multi-faceted identities and the ways in which who they are as researchers in the world have an impact on data collection, analysis, and dissemination [21]. These conversations will be supported by A) the Social Identity Map [24], a tool that helps researchers to reflect on their positionality and how it influences the research process, and B) the coin model of privilege and critical allyship [25], which will help team members to reflect on their approach to solidarity in addressing healthcare system inequities.

### Study setting

This study will comprise three separate sites in Southern Ontario, Canada (THP, HRH, and RVRHC). THP is in Mississauga (the 6th largest city in Canada), located in the Peel region of Ontario, and serves Mississauga and surrounding areas, including West Toronto. Mississauga is made up of 1.4 million residents and is described as one of the most diverse regions in Canada [26]. Just over half of Peel’s population are immigrants, and approximately half report low income. Located in one of the most diverse cities in the world, HRH is a hospital in Toronto, serving approximately 850,000 residents in the surrounding areas, including Northwest Toronto, Etobicoke, York Region, and Rexdale. Northwest Toronto and the surrounding area have one of the most racialized populations in Canada, and the community also has a high proportion of seniors aged 80 and above. RVRHC is located in Barrie, Ontario, in the Simcoe Muskoka Region, with a population of just under 600,000 [27]. Simcoe Muskoka has a rapidly aging population, for which the rate of preventable mortality is 9.2 times higher than non-aging populations in the same region. This aging population (65 years of age and older) comprises 20.8 percent of the overall population [27, 28].

These three sites, THP, HRH, and RVRHC, were selected to ensure diversity in patients, diversity in geographic location, and to capture the varied experiences of potentially marginalized groups; both the City of Toronto and Peel region where THP is located have a higher concentration of immigrant and visible minorities [29, 30].

## Materials, methods, and data analysis: Quantitative investigation

### Population

For the quantitative investigation, secondary administrative health data will be used, which will include approximately 1.8 million patients with 12 million observations. These are patients 65 years and older who were admitted to an acute care facility. Data will be excluded from patients less than 65 years of age, from those who are non-Ontario residents, and if there is missing or invalid data.

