### Building risk profiles into personas

Based on the critical risk factors identified at each risk level from the ML model, risk profiles will be further developed into personas. In this context, personas are descriptions of the characteristics and needs of a segment of the population, which then gets written into a story and enriched with experiential information from participants; personas are therefore data and experience driven and are compiled from quantitative and qualitative data.

To develop the quantitative risk profiles into personas, first, the research team will write short vignettes or descriptions depicting the characteristics of the individuals in the sub-groups from the quantitative analysis. This first iteration of the personas will be presented to participants during qualitative focus groups and interviews for feedback. To support the development of the personas, the authors have created a worksheet, which will be shared during focus groups and interviews and will depict the quantitative variables and data (see S2 Appendix); the research team anticipates that this will include blank sections due to unavailable information from the quantitative data set. During focus groups and interviews, facilitators will prompt for experiential data to address these areas. Overall, the purpose of the personas is to build on the understanding about population experiences and perspectives, and to prompt the co-design of community care packages for this population.

The personas will also be presented to team members and advisors, who will be asked to draw on their collective experiences and share their perspectives. The research team has experience developing personas from both quantitative [12] and qualitative [48] data sources. In order to look at a range of risk, to investigate what prevention of hospital-admission might look like, and also prioritize those most at risk, the research team anticipates working with 6 risk profiles: three moderate-risk and three high-risk; however, this number may be adjusted depending on the risk profiles generated and recommendations from the research team and advisors. Half of the personas will be scenarios of people in hospitals, and the other half will be personas of people in the community.

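### The model cohort holds only admitted older adults, so it cannot give the risk or drivers of a first delayed-discharge hospitalization, although the objective is worded that way and half the personas are community-based

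*Protocol article*

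**What the plan says.** **The target.** In the protocol article, objective 1 (Study objectives, design, and research questions) is about "older adults (65 years of age and older) at risk of hospitalizations that lead to a delayed discharge". The quantitative research question in the same section is to "accurately predict the risk of delayed-discharge hospitalization and identify the characteristics of older adults with such risk". The Methods paragraph of the abstract promises to identify "sub-populations of older adults (65 years old or older) at risk of hospitalization and delayed discharge". Objective 2 is about using community resources to avoid hospitalization.

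**The data.** The Population section gives "approximately 1.8 million patients with 12 million observations" and adds: "These are patients 65 years and older who were admitted to an acute care facility". Under Creating risk profiles: Quantitative data and analysis, clinical records and the outcome come from the Discharge Abstract Database (DAD). The Registered Persons Database (RPDB) adds demographic and socioeconomic characteristics. That section counts look-ahead windows of 90, 180 and 365 days from admission, sets a 2-year lookback, and describes the prediction as delayed discharge following hospitalization.

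**The use.** Under Building risk profiles into personas: "Half of the personas will be scenarios of people in hospitals, and the other half will be personas of people in the community". One stated reason for the planned range of six profiles is to look at what preventing admission might involve.

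**The concern.** In the objective, the abstract and the research question, the hospitalization is part of the event to be predicted. In the cohort, an admission is the condition for entry and the start of the clock. Time lived before any admission never enters the denominator, so the data carry no contrast between older adults who go on to a first admission and those who do not.

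What is at stake is the meaning of the main quantitative output. The ranked features and the low, medium and high groups are meant to feed the personas and, through them, the co-designed care packages. If the community personas are presented as people at risk of an avoidable first admission, they will rest on determinants estimated in people who had already been admitted. The Introduction notes that earlier work concentrated on patients already in hospital and presents upstream prevention as the gap. The cohort as described does not fully move past that restriction.

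**Working it through.** The protocol states no figure that can be reproduced on this point. The check is a comparison of sections, followed by a short illustration.

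**Step 1: who is in the denominator.**
- Abstract and objective 1: older adults at risk of a hospitalization.
- Population: older adults with an acute admission.
- Creating risk profiles: DAD records for clinical data and outcome, RPDB for covariates only. No group of non-admitted residents is described.

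**Step 2: what can be estimated.** For a person not yet admitted,

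P(delayed-discharge hospitalization) = P(admission) × P(delayed discharge | admission).

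The cohort informs the second factor. It does not inform the first factor for a first admission.

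**Step 3: what the look-ahead windows add.** The Population figures give 12 million / 1.8 million = 6.7 observations per patient, so repeat records are common. A window of up to 365 days from admission can reach a later stay. The article does not say whether the outcome is a designation in the index stay, in a later stay, or in either. The readings differ. As an illustration, take 20% delayed discharge given admission (the Introduction's approximate figure for acute patients generally, not for those aged 65 and over) and an assumed factor that raises readmission from 10% to 20%:
- index stay only: 0.20 / 0.20 = 1.0;
- later stay only: (0.20 × 0.20) / (0.10 × 0.20) = 0.04 / 0.02 = 2.0;
- either stay: [1 − 0.80 × (1 − 0.04)] / [1 − 0.80 × (1 − 0.02)] = 0.232 / 0.216 = 1.07.

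The weight that the model gives to a driver of admission therefore depends on a definition that is not stated. Under all three readings the result applies to people who have already been admitted.

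**Step 4: can the ranking differ from community risk?** Yes, in principle. With assumed values for an index-stay outcome:
- group A: 30% admission × 15% delay given admission = 4.5%;
- group B: 8% admission × 30% delay given admission = 2.4%.

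A model fitted to admitted patients ranks B above A (30% against 15%). Community risk ranks A above B (4.5% against 2.4%). This shows that a reversal is possible. It does not show that one occurs here, or how often.

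**Step 5: do the limitations cover it?** The Limitations section mentions selection bias from retrospective data and limited applicability to populations other than older delayed-discharge patients. It does not say that never-admitted older adults, who fall within the study's own stated target, are absent from the model.

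**The case against.** The strongest reply has four parts.

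1. The methods section is internally consistent: it describes delayed discharge following hospitalization and uses a cohort that fits. The research question does not contain the words in the community. On this view only the abstract and objective 1 are loosely worded. This is partly right, and it is why the remedy is mainly rewording. But objective 2 and the community personas show that the upstream reading is intended.

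2. The windows may capture readmissions, so drivers of admission are not necessarily lost. This stands. A reader might infer that the model can learn only delay within the index stay, or that a factor acting on admission alone would get no importance or even look protective. The document supports none of these: the first two hold only if later stays are excluded, which is not stated, and nothing shows the third.

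3. The protocol does not propose to report an absolute risk to a community resident. Scores are used to rank features and form groups. This also stands. A reader might divide 1 by an assumed annual admission risk of 5% to 20% and conclude that risk is overstated 20- to 5-fold. That figure only restates the assumption and concerns a quantity the plan does not report.

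4. The personas combine quantitative and qualitative input, and the Older adults and caregivers section opens recruitment to community-dwelling people with no hospitalization. This softens the consequence for the care packages. It does not put these people into the model that selects the profiles.

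**Conclusion.** The point holds in a limited form. As described, the cohort can support statements about delayed discharge among older adults with an acute admission and, if the windows are so defined, about later stays of previously admitted people. It cannot support statements about the risk or drivers of a first delayed-discharge hospitalization among never-admitted older adults, which the wording of objective 1, the abstract and the research question takes in.

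Feature rankings and risk groups may differ from those for community risk. The size is unknown: it depends on how admission risk and delay given admission vary together across older adults, and the document gives no figures on that.

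The conclusion rests on reading the Population section literally. If the observations also include non-admission records of people who were admitted at some time, selection would still depend on an admission, possibly a future one, and the conclusion would not change.

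**What to change.** 1. Restate objective 1, the quantitative research question and the Methods paragraph of the abstract as the risk of delayed discharge among older adults with an acute admission. Cost: wording, and a narrower claim.
2. State whether the 90-, 180- and 365-day outcome is a designation in the index stay, in a later stay, or in either. Cost: one sentence.
3. For the community personas, use profiles from a later-stay outcome with time zero at index discharge, and describe these personas as previously admitted people. The hospital personas can keep time zero at admission. Cost: a small analysis change on DAD records the study already uses.
4. Add to the limitations that never-admitted older adults are not represented in the model, so the community personas do not describe risk of a first admission. Cost: one sentence.

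The Recruitment section says recruitment had not begun in August 2024 and was expected from about December 2024. On the article's own timeline, the profiles could be settled before participants see the personas.

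A cohort of all registered residents aged 65 and over, with an index date not tied to admission, would answer the question as now worded. It is optional. The DAD, the only clinical source named, gives no acute-care lookback for people who were never admitted, so this route depends on other clinical data being available for them.

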### Data sources

Secondary administrative health data will be used from data housed at the Institute for Clinical Evaluative Sciences (ICES) in Ontario, Canada. ICES is an independent, non-profit research institute funded by an annual grant from the Ontario Ministry of Health and the Ministry of Long-Term Care. As a prescribed entity under Ontario’s privacy legislation, ICES is authorized to collect and use healthcare data for the purposes of health system analysis, evaluation, and decision support. The use of the data in this project is authorized under section 45 of Ontario’s Personal Health Information Protection Act (PHIPA) and is approved by the ICES privacy office; as such, it does not require further review by a research ethics board. Secure access to these data is governed by policies and procedures approved by the Information and Privacy Commissioner of Ontario. These datasets are linked using unique encoded identifiers and analyzed at ICES.

